### Confidentiality

To maintain complete confidentiality, participant identification data will not be included in questionnaires or computer software. Unique codes are used for participant identification. Identifiable information is recorded separately and securely stored. Access is limited to authorized individuals, with exceptions granted for valid justifications.

### Data analysis

The data obtained will be analyzed using the double data entry approach in SPSS software version 24. Descriptive statistics, including frequency (percentage) for categorical data and mean (standard deviation) for normally distributed data, as well as median (interquartile range) for non-normally distributed data, will be used to describe socio-demographic and obstetrics characteristics. The normality of the data will be assessed using the Kolmogorov-Smirnov test.

In the bivariate analysis, ANCOVA and the chi-square test will be employed to compare the means of variables related to diabetes self-care activities, diabetes management self-efficacy, pregnancy experience, satisfaction with perinatal care, breastfeeding performance at 6 weeks postpartum, and the frequencies of preterm delivery, cesarean section delivery, and neonatal hospitalization between the two groups. In the multivariate analysis, the general linear model will be utilized, controlling for socio-demographic and obstetric characteristics, to further explore the relationships among the variables mentioned above.

### Qualitative phase (phase 2)

#### Study design

In the qualitative phase of this study, the research method utilized is qualitative content analysis with a conventional approach [40].

#### Specific objectives (qualitative phase)

The specific objectives of the second phase are to explore the understanding of pregnant women with diabetes regarding the impact of implementing the Centering Pregnancy group care model on their care process.

#### Eligibility criteria

Participants who are part of the Centering Pregnancy group care model and express willingness to participate in the study.

#### Sample size and sampling

The selection of participants will be based on the objective of the study, which takes place after the completion of training sessions. Maximum diversity will be taken into consideration regarding individual, social, and maternal characteristics. The sampling process will continue until information saturation is achieved, which means that no new information or codes will be obtained.

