## Study design

This research is a study of a convergent parallel mixed methods, and its paradigm is pragmatism. The present study will be conducted in three phases: quantitative, qualitative, and the combination of both quantitative and qualitative phases. In this mixed design, qualitative and QUAN quantitative data will be collected and analyzed simultaneously and independently. Both types of data will have equal priority and value (QUAL + QUAN). Data analysis will be performed separately, and the results will be integrated during the data interpretation stage. The discussion will focus on the degree and extent of convergence between quantitative and qualitative data [24, 25] (Fig. 1).

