#### Specific objectives

The specific objectives of the quantitative phase are as follows:

To compare the mean scores of diabetes self-care activities in weeks 36–39 of pregnancy between the intervention and control groups (receiving Centering Pregnancy group care model and receiving routine care, respectively), while controlling for baseline scores.To compare the mean scores of self-efficacy in weeks 36–39 of pregnancy between the intervention and control groups (receiving Centering Pregnancy group care model and receiving routine care, respectively), while controlling for baseline scores.To compare the mean scores of pregnancy experience in weeks 36–39 of pregnancy between the intervention and control groups (receiving Centering Pregnancy group care model and receiving routine care, respectively), while controlling for baseline scores.

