#### Eligibility criteria

The study includes pregnant women who have gestational diabetes mellitus (GDM) or type 2 diabetes and are at least 24 weeks pregnant. They must be able to attend group sessions in Tabriz city for a duration of 8 weeks before childbirth. However, the study excludes women with multiple pregnancies, major fetal anomalies, concurrent medical conditions, psychiatric disorders, and advanced or complicated diabetes. These criteria are important for ensuring the study focuses on a specific group of participants who meet the requirements and can provide valuable insights into the research objectives.

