#### Intervention

The intervention group will participate in an 8-week program consisting of group sessions held every 2 weeks, with each session lasting approximately two hours. These sessions will be led by a midwife who is a PhD student in midwifery and an obstetrician, and the group will consist of 2 to 10 women. The content of each session will be based on the curriculum and materials of the centering pregnancy program, which have been reviewed and approved by the obstetrician and nutritionist.

At the start of each session, the midwife, assisted by the researcher, will conduct measurements of weight, blood pressure, and blood glucose levels using a glucometer. This assessment process will take approximately 30 min. The remaining time, around 60 to 90 min, will be dedicated to group discussions focused on predetermined topics that are relevant to the participants’ needs.

Session 1: The first session will provide diabetes education, covering the risks of diabetes for both the mother and the fetus, the importance of self-monitoring, and nutrition education. This will include introducing food groups, emphasizing the significance of meal control, providing information on food labels, and facilitating discussions on pregnancy-related concerns and coping strategies.Session 2: The second session will continue with diabetes education, focusing on the importance of exercise. Additionally, there will be discussions on pregnancy-related topics such as pain relief during labor and addressing issues of intimate partner violence.Session 3: The third session will address postpartum diabetes and what to expect during the postpartum period. Participants will also receive information on the importance of glucose tolerance testing. Pregnancy-related topics will include discussions on expectations during labor and delivery, as well as contraception.Session 4: The fourth session will emphasize diabetes education related to lifelong health monitoring and the risk of diabetes for offspring. Additionally, there will be discussions on pregnancy-related topics such as newborn care, including sleeping, proper usage of car seats, and feeding (Table 1).

**Table 1 Tab1:** Curriculum for group prenatal care in women with diabetes

Sessions	Pregnancy Titles	Diabetes Titles

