### Combination of both quantitative and qualitative phase (phase 3)

#### Specific objectives

The specific combined objective is to provide a better understanding of the impact of implementing the Centering Pregnancy group care model on maternal and infant outcomes by elucidating women’s perception of the model’s influence on their care process.

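### Interviews held only in the intervention arm are triggered by the end of the sessions and not placed after the 36–39 week questionnaires, so some can precede the self-reported primary outcomes

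*Protocol article*

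**What the plan says.** **Interview timing.** The qualitative phase, under Sample size and sampling, gives one time marker: "The selection of participants will be based on the objective of the study, which takes place after the completion of training sessions". It gives no latest time and no order relative to the primary questionnaires.

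**Who is interviewed.** The Eligibility criteria of the qualitative phase read: "Participants who are part of the Centering Pregnancy group care model and express willingness to participate in the study". Controls are not interviewed. The number is left to saturation. Data collection in that phase describes one-to-one, semi-structured interviews in which open questions are followed by probing ones. The phase's objective is what pregnant women understand of the model's effect on their care.

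**Primary assessment.** The first quantitative objective is "To compare the mean scores of diabetes self-care activities in weeks 36–39 of pregnancy between the intervention and control groups", adjusted for baseline. The same window applies to self-efficacy and pregnancy experience.

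**Entry and programme.** Women "are at least 24 weeks pregnant" at entry, and "They must be able to attend group sessions in Tabriz city for a duration of 8 weeks before childbirth". The intervention is an "8-week program consisting of group sessions held every 2 weeks", with four sessions listed.

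**How the two strands relate.** Study design states that "qualitative and QUAN quantitative data will be collected and analyzed simultaneously and independently".

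**Blinding and questionnaire completion.** Randomization and blinding says that only the data analyst is blinded. Management of missing data says that the research team completes the questionnaires by interview.

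**The concern.** The interview is a substantial extra contact. A member of the trial team sits with a woman and asks her to reflect at length on what the group model did for her care. If this happens before her 36–39 week questionnaires, the same team then asks her to report self-care, self-efficacy and pregnancy experience. Reflection may prompt self-care, or may make favourable answers more likely. Controls have no equivalent contact.

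Any lift would be counted as an effect of group care. Randomization does not protect against it, because it arises after allocation and in one arm only. Blinding the analyst does not remove it either, because it enters when the data are collected. Strengths and limitations already concedes that self-report may carry social desirability bias, and this would add an avoidable source of it.

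**Working it through.** The point turns on the calendar. The plan has no figure of its own here to reproduce.

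**Inputs**
- Earliest entry: 24 weeks, with no upper limit stated (quantitative Eligibility criteria).
- Programme: four fortnightly sessions in 8 weeks (Intervention). If the first session is at week 0, the sessions fall at weeks 0, 2, 4 and 6, so the last is 6 weeks after the start. If the full programme length is counted, it ends 8 weeks after the start.
- Primary window: 36–39 weeks (quantitative Specific objectives).
- Assumption: the first session takes place at the starting week shown. If a woman waits for a group to form, her start is later and her gap shorter.

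**Formulas**
- Last session = starting week + 6, or + 8.
- Gap before the window opens = 36 − last session.
- Gap before the window closes = 39 − last session.

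| Start (weeks) | Last session (+6 / +8) | Gap to week 36 | Gap to week 39 |
|---|---|---|---|
| 24 | 30 / 32 | 6 / 4 | 9 / 7 |
| 26 | 32 / 34 | 4 / 2 | 7 / 5 |
| 28 | 34 / 36 | 2 / 0 | 5 / 3 |
| 30 | 36 / 38 | 0 / −2 | 3 / 1 |

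For a 24-week start there are 4–6 clear weeks between the last session and the opening of the window. For a 28-week start there are 0–2. From a 30-week start the sessions end inside the window. No clear gap then remains, although the order of interview and questionnaire within the window is still not fixed.

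**Does the text close the gap?** Three statements bear on it.
- Sample size and sampling sets only an earliest time. An interview straight after session four complies.
- Study design has the two strands collected simultaneously, which does not put one before the other.
- The abstract and the qualitative objective speak of pregnant women's understanding, which fits interviews before birth.

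None of these requires the questionnaires to come first, so early interviews are permitted for women who start at about 24–28 weeks.

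**Size of any bias.** If k of the n women in the arm are interviewed before assessment, and each such interview shifts the score by b, the arm mean moves by (k/n) × b. The document gives n (50 randomized per group) but neither k nor b. The size therefore cannot be derived.

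**The case against.** **The order is left open.** The strongest reply is that the plan nowhere says the interviews come before the assessment. It sets a lower bound only. Interviews after the questionnaires, or at the same visit, comply equally well, and simultaneous collection describes a convergent parallel design rather than a visit schedule. An article may also leave the interview calendar to the full protocol. This stands to the extent that the early contact is a possibility and not a stated step. It does not dispose of the point, because the article does state a trigger, and that trigger is the end of the sessions and not the completion of the primary outcome. A researcher who follows it faithfully can interview too early.

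**Few women are exposed.** The 4–6 weeks apply to the earliest entrants, and only a purposive subset of one arm is interviewed. This is correct and limits the weight of the point.

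**The interview is exploratory.** The document describes open questions, with no teaching or feedback, so nothing supports a charge that women are coached. The remaining concern is reflection and social desirability, which needs no coaching.

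**A stronger reading: phase 3 fails.** A reader might infer that interviews held before birth cannot serve the phase 3 aim "to provide a better understanding of the impact of implementing the Centering Pregnancy group care model on maternal and infant outcomes". The documents do not support this. The same sentence says that the aim is to be reached through women's perceptions of how the model influenced their care, and interviews held after the sessions can supply these. Preterm birth, cesarean section and NICU admission come from the outcomes checklist, and breastfeeding comes from a questionnaire. The strands are joined at interpretation. Interviews before birth would lack women's accounts of birth and the newborn, but the objective does not ask for those.

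**Conclusion.** The point holds as a matter of ordering. The plan permits an in-depth contact in one arm, with the trial team, before unblinded self-report primary outcomes that the team also collects. For a 24-week start the opening is 4–6 weeks before week 36. It narrows to 0–2 weeks at 28 weeks and is closed by 30 weeks. This rests on counting the last session at 6 to 8 weeks after the start, and on the first session following promptly on entry.

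The plan does not fix that any woman will be interviewed early. A reader might be tempted to express the bias as a share of the planned 0.6-point difference. Any such percentage would come wholly from an assumed number of early interviews and an assumed shift per interview, so none is offered. The change is worth making because it costs almost nothing and removes a route to bias that the analysis cannot correct.

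**What to change.** In the qualitative phase, under Sample size and sampling, add to the existing trigger that a woman is interviewed only once her 36–39 week primary questionnaires are complete. An interview at the same visit, straight after the questionnaires, is acceptable.

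This is a wording change. It needs no extra visit and keeps interviews during pregnancy possible. The downside is that early entrants recall the sessions a little later: for a 24-week start, at least 4–6 weeks after the last session.

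Moving the interviews to 6 weeks postpartum is not needed for this purpose. It would let women describe birth and the newborn, but the women would no longer be pregnant and recall of the sessions would be later still. That is a choice for the investigators.

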#### Data collection

As part of the qualitative research methodology, in-depth and semi-structured individual interviews will be conducted. Open-ended questions will be utilized during these interviews to allow for rich and detailed responses from participants. The interviews will take place in natural settings, provided suitable conditions exist, and participants express their willingness to participate.

Prior to this phase, the research team will collaborate to develop the interview guide, ensuring the collection of valid data and alignment with the research objectives. The interviews will commence with predetermined questions, and as the dialogue progresses, probing and exploratory questions will be employed to gain a more profound understanding of the participants’ experiences [41]. To ensure accurate documentation, the researcher will record non-verbal cues, such as vocal intonation, facial expressions, and body language, on a dedicated record sheet, noting the time and location of each interview.

#### Data analysis

The qualitative content analysis method will be used for data analysis in this study [42], involving categorization, coding, and identification of themes and patterns in the textual data. This analysis aims to uncover hidden themes and patterns in the participants’ data. Categories will be created to group content with common characteristics, and further subcategories may be formed. Themes will capture the “how” aspect of the data, representing meaningful threads within the coded data or categories at different interpretive levels. The interview notes will be transformed into categories and themes as part of the analysis process. The organization of interview texts and codes will be facilitated through the utilization of MAXQDA software.

To ensure the quality of the qualitative research, five criteria are commonly used: credibility or acceptability, dependability, confirmability, transferability, and authenticity. These criteria help evaluate the accuracy and trustworthiness of the research findings [43, 44].

### Combination of both quantitative and qualitative phase (phase 3)

#### Specific objectives

The specific combined objective is to provide a better understanding of the impact of implementing the Centering Pregnancy group care model on maternal and infant outcomes by elucidating women’s perception of the model’s influence on their care process.

#### Data integration

Data integration can be achieved through concurrent designs, including concurrent triangulation, concurrent nested, and concurrent transformative. In concurrent triangulation, both qualitative and quantitative data are collected and analyzed simultaneously, with equal priority given to both types of data. Data analysis is typically conducted separately, and integration occurs during the interpretation phase [45]. The current research involves collecting numerical data for the quantitative phase and textual data for the qualitative phase. The collected data will be analyzed separately using SPSS and content analysis, respectively. The findings from both phases will be integrated, and a comprehensive interpretation will be presented.

#### Ethics approval and consent to participate

The present study followed ethical guidelines, including the Helsinki Declaration and national principles. Approval was obtained from the ethics committee of Tabriz University of Medical Sciences (IR.TBZMED.REC.1402.652/ 2023-12-04). The quantitative phase, a randomized controlled clinical trial, is registered in the Iranian Clinical Trial Registration Centre (IRCT20120718010324N80/ 2024-01-03). Informed written consent will be obtained from all participants, ensuring confidentiality and privacy. Participants have the right to withdraw from the study at any stage without consequences, and non-cooperation is voluntary without affecting their services.

## Discussion

The WHO recommends the provision of health system interventions to improve the use and quality of antenatal care in order to enhance perinatal outcomes and women’s experience of care [46].

Antenatal care can be delivered through individual or group-based approaches [47]. In low-risk pregnant women, group antenatal care has been shown to yield improvements in stress levels, self-confidence, knowledge, motivation for healthy behaviors during pregnancy, and active engagement in healthcare practices [48].

Women diagnosed with diabetes during pregnancy often experience shock and anxiety. They may also feel guilt regarding the potential effects on their unborn child. These feelings of anxiety and remorse can have a negative impact on their overall pregnancy experience [49, 50]. It has been shown that group-based antenatal care has a positive impact on the psychosocial well-being of women with higher levels of stress or lower personal coping resources [51].

Group-based antenatal care, specifically the Centering Pregnancy model, has been associated with higher utilization of long-acting reversible contraception and increased likelihood of postpartum oral glucose tolerance testing in women with diabetes. However, no significant differences in adverse outcomes were found between group-based and individual care, warranting further research [19].

Lifestyle interventions can enhance women’s self-management of diabetes and reduce stress and anxiety during pregnancy [52, 53]. Education regarding GDM control, healthy eating, and physical activity are practical interventions that improve self-care and empower women with diabetes [54, 55]. Centering Pregnancy group prenatal care model, has demonstrated encouraging outcomes in improving nutrition and lifestyle among women with diabetes [32]. However, existing studies on the Centering Pregnancy model have predominantly focused on healthy pregnant women, and there is a lack of qualitative or mixed-methods research specifically investigating its effectiveness in pregnant women with diabetes [48, 56–58]. Nevertheless, it is recommended to consider implementing this care model for high-risk women to enhance a comprehensive understanding and achieve better outcomes [14, 59].

### Strengths and limitations

The present study will be the first of its kind in Iran to implement and evaluate the Centering Pregnancy group care model in pregnant women with diabetes using a mixed methods approach. Other strengths include the use of randomization methods to prevent selection bias in the quantitative phase and the validation of the SDSCA questionnaire, which measures self-care activities, in Iranian women with GDM and pregnant women with type 2 diabetes for the first time. This questionnaire can serve as a standardized and widely used tool for assessing self-care activities in these women in future studies. Furthermore, exploring the experiential understanding of women with diabetes in pregnancy regarding this group care model can provide healthcare professionals with greater knowledge about women’s experiences with diabetes and inform practical interventions for reducing the risk of diabetes in women.

The study has several limitations. Firstly, the reliance on self-report measures, such as the SDSCA questionnaire, may introduce recall bias or social desirability bias. Additionally, there are constraints associated with financial limitations the ability to assess long-term outcomes. Another limitation is the lack of blinding among the providers and participants, which is inherent to the nature of the intervention and could potentially bias the results. However, the statistical analyst will be unaware of the group assignments during the analysis, minimizing this bias. Furthermore, since this type of care is being implemented for the first time in Iran, it relies on the cooperation and acceptance of women, which could lead to attrition bias in the 8-week intervention. Lastly, the generalizability of the study’s findings is limited to women with gestational diabetes and low-risk overt diabetes.

